### Sample Size Calculation

The sample size was calculated for the primary outcome, the NDI, based on detecting a clinically meaningful between-group difference of 7.5 points, which is consistent with previous studies on the responsiveness of the NDI. Assuming a standard deviation of 10.58 points, a 2-sided significance level of .05, and 80% statistical power, the required sample size was 32 participants per group. To account for an anticipated 10% (3/32) loss to follow-up, the final target sample size was increased to 35 participants per group, resulting in a total sample of 70 participants.

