### Data Analysis

Data will be analyzed using SPSS (version 28.0; IBM Corp) and will follow the intention-to-treat principle, whereby all randomized participants will be analyzed in the groups to which they were originally assigned, regardless of treatment adherence or completion. Additionally, a per-protocol analysis will be conducted including participants who complete at least 80% (5/6) of the in-person treatment sessions. All analyses will be conducted by a statistician blinded to group allocation.

Descriptive statistics will be calculated for all variables. Continuous variables will be presented as mean (SD) or median (IQR), depending on the data distribution, while categorical variables will be expressed as frequencies and percentages.

Baseline comparability between groups will be assessed using independent Student *t* tests for normally distributed continuous variables, Mann-Whitney *U* tests for nonnormally distributed variables, and chi-square tests for categorical variables. Normality will be evaluated using the Kolmogorov-Smirnov test and visual inspection of histograms.

A statistically significant group × time interaction will be interpreted as evidence of differential treatment effects over time. To evaluate the effects of the intervention over time and between groups, linear mixed-effects models will be used, including group (experimental vs control), time (baseline, postintervention, and 2-mo follow-up), and the group × time interaction as fixed effects, with participants included as random effects. This approach allows appropriate handling of repeated measures and missing data.

If model assumptions are not met, appropriate nonparametric alternatives (eg, Friedman test for within-group comparisons and Mann-Whitney *U* test for between-group comparisons with adjusted post hoc analyses) will be applied. Adjustment for multiple comparisons among secondary outcomes will be performed using the Holm-Bonferroni procedure.

Missing data will be handled using multiple imputation methods under the assumption of missing at random. Sensitivity analyses will be conducted to assess the robustness of the findings. Dropouts and losses to follow-up will be reported and compared between groups. Twenty imputed datasets will be generated using multiple imputation procedures.

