The primary end point will be the between-group difference in change in NDI scores from baseline to postintervention. Postintervention was defined as 1 day after completion of the sixth treatment session. Age, sex, and baseline NDI values will be explored as potential covariates if baseline imbalance is detected. Secondary outcomes will include changes in Visual Analog Scale, McGill Pain Questionnaire, quality of life SF-36, Tampa Scale of Kinesiophobia, cervical range of motion, Pittsburgh Sleep Quality Index, PCS, pressure pain threshold, cervical isometric strength, and cervical flexor endurance. Effect sizes (eg, Cohen *d*) will be calculated to assess the magnitude of differences.

Additionally, the clinical relevance of the findings will be assessed by comparing observed changes with established minimal clinically important differences. Based on previous studies in patients with neck pain, a change of approximately 7.5 points on the NDI and 1.5 points on pain intensity scales has been considered clinically meaningful and will be used to aid the interpretation of clinical relevance [49]. For other secondary outcomes, where established minimal clinically important differences are available, these will be considered to aid the interpretation of clinical significance.

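### Adjustment for baseline NDI depends on a detected imbalance and has no stated form; it should be prespecified and unconditional

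*Protocol article*

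**What the plan says.** All of the following is in the Data Analysis section of the protocol article.

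- End point: "The primary end point will be the between-group difference in change in NDI scores from baseline to postintervention".
- Model: a linear mixed-effects model with group, "time (baseline, postintervention, and 2-mo follow-up), and the group × time interaction as fixed effects", "with participants included as random effects". Baseline NDI is therefore one of the response values, and each arm has its own free baseline mean.
- Baseline checks: "Baseline comparability between groups will be assessed using independent Student" *t* tests, with Mann-Whitney and chi-square tests for other kinds of variable. No threshold is given for calling a difference an imbalance.
- Covariates: "Age, sex, and baseline NDI values will be explored as potential covariates if baseline imbalance is detected". How they would enter the model is not stated.
- Missing data: "Twenty imputed datasets will be generated using multiple imputation procedures", so each data set analysed after imputation is complete.

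The Safety Considerations section adds a commitment to leave the analyses unchanged once the first participant is registered.

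**The concern.** Two features of the rule work against the primary comparison.

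First, the decision to adjust waits on the observed baseline data. In a randomised trial a baseline difference is due to chance, so a significance test of it says nothing useful about whether baseline NDI should be in the model. What matters is how strongly baseline predicts the later score, and that can be expected in advance. A test-triggered rule leaves the primary model open until the data are seen, and in most trials it omits the covariate.

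Second, when the rule does fire, it may not do what it is for. The model already treats baseline as an outcome. If baseline NDI is simply added as a further main effect, the contrast that defines the primary end point does not move.

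At stake are precision in a trial of 70 participants and, after an unlucky randomisation, an estimate still carrying regression to the mean that adjustment would remove.

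**Working it through.** **Inputs.** From Sample Size Calculation: "detecting a clinically meaningful between-group difference of 7.5 points"; "Assuming a standard deviation of 10.58 points"; two-sided 5% level; 80% power; 32 per group, raised to 35. Not given in the article, and assumed here: the correlation r between baseline and postintervention NDI (0.3 to 0.8), equal variances at the two visits, and a p<0.05 trigger for imbalance.

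**1. The plan's own figure.** n per group = 2 × (1.960 + 0.842)² × (10.58/7.5)² = 2 × 7.85 × 1.990 ≈ 31.2, so 32. Power at 32 is 80.9% by the normal approximation and 79.7% by the noncentral *t*. The stated figure reproduces.

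**2. How often the rule fires.** With a 5% test, baseline NDI enters in about 5% of randomised trials. At least one of three independent covariates enters in 1 − 0.95³ ≈ 14%.

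**3. What a main effect does in the stated model.** For participant i in group g, with baseline NDI b as a main effect:

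- mean at baseline = μ₀ + γg + βb
- mean at postintervention = μ₁ + γg + δg + βb
- post minus baseline = (μ₁ − μ₀) + δg

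The term βb cancels, and so would age or sex. With complete data the estimate of δ is the raw between-group difference in mean change, with or without the covariate.

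This was checked by simulation: 35 per arm, true effect −7.5, experimental arm about 5 points higher at baseline, random-intercept fits, 200 trials per setting. Five points is about the smallest difference that reaches p<0.05 at 35 per arm if the baseline SD is 10.58. Adding baseline NDI, alone or with age and sex, moved the contrast by less than 10⁻¹². The ratio of standard errors averaged 0.999 to 1.000.

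**4. What is left uncorrected after a chance imbalance.** The expected change contrast is −7.5 − (1 − r) × 5.

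| r | Expected change contrast | Simulated, with or without main effect | Simulated, common baseline mean |
|---|---|---|---|
| 0.5 | −10.0 | −10.0 (SE 2.50) | −7.6 (SE 2.18) |
| 0.7 | −9.0 | −8.9 (SE 1.95) | −7.4 (SE 1.80) |

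With 10% dropout and no imputation, the main effect moved single-trial estimates by at most about 0.4 points, left the average where it was, and reduced the SE by about 1 to 2%.

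**5. Precision.** With single-visit variance σ², the between-participant variance is 2σ²(1 − r) for the change score and σ²(1 − r²) after baseline adjustment. The ratio is (1 + r)/2, a reduction of (1 − r)/2. The last two columns take 10.58 as the SD of change, the reading that matches the end point, under which the unadjusted contrast needs 32 per group and has 81% power.

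| r | Variance reduction | Excess SE of unadjusted contrast | n per group for 80% if adjusted | Power at 32 if adjusted |
|---|---|---|---|---|
| 0.3 | 35% | 24% | 21 | 94% |
| 0.5 | 25% | 15% | 24 | 91% |
| 0.7 | 15% | 8% | 27 | 87% |
| 0.8 | 10% | 5% | 29 | 85% |

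**The case against.** The strongest reply is that the article says only that covariates will be explored. It does not say they enter as main effects alone. A baseline-by-time term, or ANCOVA of the postintervention score, would change the contrast, and such detail may sit in an analysis plan that is not shown. This stands, and it limits the second part of the point: the cancellation holds for main-effect entry, and a reader should not infer that the remedy does nothing under every form. It does not touch the first part, because the conditional trigger is stated in the article itself.

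The planned contrast is also not invalid. It is unbiased over randomisation, and it does subtract baseline. That stands too.

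Three stronger readings are tempting but not supported.

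- *The trial is underpowered.* If 10.58 were a single-visit SD, the unadjusted change score would have 66% power at r = 0.3 and 72% at r = 0.4 with 32 per group. That needs both an SD reading the article does not state and an assumed r below 0.5. If 10.58 is the SD of change, the stated 80% holds.
- *The change score is the least efficient analysis.* Its variance is 2σ²(1 − r), against σ² for unadjusted postintervention scores, so it is the better of those two whenever r exceeds 0.5 (0.6σ² against σ² at r = 0.7).
- *The standard error is wrong because participant random effects force equal correlations.* The article does not say random intercept only, and covariance structure is ordinary analysis-plan content. Even under a random intercept, unequal correlations need not distort the result: with 0.6 (baseline-post), 0.5 (baseline-follow-up) and 0.7 (post-follow-up) the mean is 0.6, and the contrast variance 2(1 − 0.6) = 0.8 is correct.

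Finally, the Safety Considerations commitment weighs against rewriting the primary model now. It means that the change must be dated and disclosed. It does not remove the benefit, and a data-triggered covariate rule itself leaves the model open after registration.

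**Conclusion.** The point holds as an improvement that should be made, not as a flaw that invalidates the analysis. The trigger makes the primary model data-dependent and will usually omit baseline NDI. The form of adjustment is unstated, and the simplest form would leave the primary contrast unchanged in complete or imputed data. The cost of not adjusting is a variance larger than necessary: adjustment would cut it by about 35% at r = 0.3, 25% at r = 0.5, 15% at r = 0.7 and 10% at r = 0.8. These sizes assume equal variances and a value of r that the article does not supply. The 5% firing rate assumes a p<0.05 trigger. The direction of the gain holds for any r below 1 under equal variances and does not depend on which SD 10.58 represents.

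**What to change.** In a dated amendment made before unblinding, and disclosed openly against the commitment in Safety Considerations, state that the primary analysis always adjusts for baseline NDI whatever the baseline comparison shows. Either of two forms will do:

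- postintervention and 2-month NDI as the responses, with group, time, group × time, baseline NDI and baseline NDI × time as fixed effects; or
- all three visits as responses, with the two arms constrained to a common baseline mean.

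Drop baseline significance tests as a trigger. Decide in advance whether age and sex are in or out. Apply the same rule to the continuous secondary outcomes, each with its own baseline value. The unadjusted change contrast can be kept as a sensitivity analysis, for continuity with the published text. If unblinding has already taken place, the adjusted analysis should be reported as post hoc.

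The cost is a few lines of text and one or two degrees of freedom for baseline NDI. No new data are needed.

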**Inclusion criteria**
Men and women aged 30-68 years.Chronic nonspecific neck pain lasting >3 months.Resting pain score ≥3 on the Numeric Pain Rating Scale.Not receiving other physical therapy treatment.Able to understand the study procedures and provide informed consent.

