### Data Collection and Outcome Measures

At the start of the study, demographic and clinical data will be collected, and all outcome measures will be assessed at 3 time points: baseline (preintervention), immediate posttreatment (1 d after the last session), and short-term follow-up (2 mo postintervention). Outcome assessments will be performed by a blinded evaluator using standardized procedures and calibrated instruments to improve measurement reliability and reproducibility.

The primary outcome is the Neck Disability Index (NDI), a 10-item questionnaire assessing activities of daily living. Each item is scored on a 0‐5 Likert scale. Total scores are converted to percentages (0%‐100%), with 0% indicating full independence and 100% indicating complete dependence [38,39].

Secondary outcome measures include the following:

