Visual Analog Scale: Used to assess pain intensity, participants will mark their pain level on a 100-mm horizontal line, with 0 mm representing “no pain” and 100 mm representing the “worst imaginable pain” [40].McGill Pain Questionnaire: A self-administered multidimensional measure of pain widely used across different patient populations, assessing both the quality and intensity of pain. It includes 3 components: sensory-discriminative, cognitive-evaluative, and affective-motivational [41].SF-36 (Short Form-36 Health Survey) Questionnaire: Used to assess quality of life, the SF-36 consists of 36 items across 8 subscales: physical functioning, role physical, bodily pain, general health, vitality, social functioning, role emotional, and mental health. Scores range from 0% to 100%, with higher scores indicating better perceived quality of life [42].Tampa Scale for Kinesiophobia: A 17-item questionnaire measuring fear of movement and (re)injury. It uses a 4-point Likert scale ranging from “strongly disagree” to “strongly agree” [43].Cervical range of motion: Measured using a digital goniometer (Pro Motion Capture, Werium). Participants will sit comfortably in a chair with feet flat on the floor, hips and knees at 90°, and buttocks supported against the backrest [44].Pressure algometry at MTrPs: A Wagner FPI 10 algometer with a rubber tip and dial will measure pressure applied to MTrPs in 0.5 kg increments. Evaluated muscles include the occipitofrontalis, splenius capitis, sternocleidomastoid, anterior, middle, and posterior scalenes, upper, middle, and lower trapezius, supraspinatus, infraspinatus, and multifidus at C6 [45].Pittsburgh Sleep Quality Index: Measures sleep quality and consists of 24 items, of which 19 are self-administered and 5 are for cohabitants. Items are grouped into 7 components: subjective sleep quality, sleep latency, sleep duration, habitual sleep efficiency, sleep disturbances, use of sleep medication, and daytime dysfunction. A 4-point Likert scale (0=“rarely,” 1=“sometimes,” 2=“often,” 3=“almost always”) is used, with items 2 and 5 reverse scored. Total scores range from 0 to 21, with higher scores indicating more severe sleep problems [45].Pain Catastrophizing Scale (PCS): A self-administered questionnaire assessing pain catastrophizing in clinical and nonclinical populations. Catastrophizing is defined as an exaggerated negative orientation toward noxious stimuli and influences pain perception and coping. The PCS consists of 13 items evaluating rumination, magnification, and helplessness, scored on a 5-point scale [46].Cervical isometric strength test: Maximum isometric strength of the neck extensors will be measured using a handheld dynamometer. Participants will sit with their feet flat on the floor, hips and knees at 90°, and neck in a neutral position. The handheld dynamometer will be held against the occiput with both hands, and participants will resist cervical extension isometrically for 3 seconds until maximum force is achieved [47].Cervical flexor endurance test: To assess maximal isometric strength of cervical flexors, participants will lie supine performing a double chin tuck and maintain this position. They will lift their head approximately 2.5 cm off the table and hold for as long as possible, while the evaluator measures endurance time. The test will end if the participant loses the position for more than 1 second or requests to stop due to pain or fatigue [48].

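### The pain threshold of 1.5 points does not fit the 100-mm VAS, and the plan does not say whether the thresholds apply within arms or between them

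*Protocol article*

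**What the plan says.** The Data Analysis section of the protocol article states that "the clinical relevance of the findings will be assessed by comparing observed changes with established minimal clinically important differences". It then gives two figures, citing previous studies: "a change of approximately 7.5 points on the NDI and 1.5 points on pain intensity scales has been considered clinically meaningful". Their role is limited: they "will be used to aid the interpretation of clinical relevance".

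The scales are described under Data Collection and Outcome Measures:

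- **Pain (VAS):** "participants will mark their pain level on a 100-mm horizontal line", running from 0 mm to 100 mm.
- **NDI:** there are 10 items. "Each item is scored on a 0‐5 Likert scale". "Total scores are converted to percentages", from 0% to 100%.

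A numeric pain scale appears only as an entry criterion ("Resting pain score ≥3 on the Numeric Pain Rating Scale"), and its range is not given. The McGill questionnaire is also said to cover intensity, but no 0-10 score is described for it.

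Sample Size Calculation is based on "detecting a clinically meaningful between-group difference of 7.5 points", with an SD of 10.58 points, and arrives at 32 per group. Data Analysis defines the primary end point as the between-group difference in NDI change from baseline to postintervention.

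**The concern.** Two things are left loose in a passage that will shape how the results are described.

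**Unit of the pain threshold.** The outcome is recorded in millimetres from 0 to 100, while the threshold is 1.5 points on unspecified pain scales. A reader who applies it to the recorded score would call a 1.5-mm shift clinically meaningful.

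**Quantity compared with the threshold.** Observed changes could mean the change in one arm or the difference in change between arms. The same 7.5 is called a change in Data Analysis and a between-group difference in Sample Size Calculation. Both arms receive the same exercise program, which the Introduction credits with improving function and reducing pain. Single-arm change also contains natural recovery and regression to the mean. The article says in several places that its question is the added value of EDN, and only the between-group contrast answers that.

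At stake is a published statement of clinical relevance that rests on too low a bar for pain, or on a single-arm change for the NDI.

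A smaller gap is that neither 7.5 nor 10.58 is labelled as raw (0-50) or percentage NDI points.

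**Working it through.** **1. The plan's own sample size.** Inputs from Sample Size Calculation: difference 7.5, SD 10.58, two-sided alpha 0.05, power 80%.

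n per group = 2 × [(1.96 + 0.8416) × 10.58 / 7.5]² = 31.24, rounded up to 32.

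The stated 32 is reproduced by the normal approximation. The standardized difference is 7.5 / 10.58 = 0.71.

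**2. Pain threshold against the recorded scale.** The VAS range is 100 mm.

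| Reading of 1.5 | In mm | Share of range |
|---|---|---|
| As recorded (mm) | 1.5 | 1.5 / 100 = 1.5% |
| Points on a 0-10 scale (assumption) | 1.5 × 10 = 15 | 15% |

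The two readings differ by a factor of 10.

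To see what the literal reading means in practice, assume a VAS SD of 15 to 25 mm (not in the documents) and 32 per group. The standard error of a difference in means is SD × √(2/32) = SD / 4, or 3.75 to 6.25 mm. With no true effect, the chance that the observed difference favors EDN by at least the threshold is:

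| Assumed SD | SE | P(≥ 1.5 mm) | P(≥ 15 mm) |
|---|---|---|---|
| 15 mm | 3.75 | 1 − Φ(0.40) = 34% | 1 − Φ(4.0) = 0.003% |
| 20 mm | 5.00 | 1 − Φ(0.30) = 38% | 1 − Φ(3.0) = 0.13% |
| 25 mm | 6.25 | 1 − Φ(0.24) = 41% | 1 − Φ(2.4) = 0.8% |

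A 1.5-mm bar would therefore hardly separate benefit from chance.

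**3. Within-arm or between-group.** The primary contrast is (change in the EDN arm) − (change in the exercise arm). If each arm improves by exactly 7.5, both reach the threshold and the contrast is 7.5 − 7.5 = 0. Meeting 7.5 within an arm therefore says nothing about the added effect of EDN.

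**4. NDI unit.** The raw maximum is 10 × 5 = 50. If 7.5 is already on the percentage score, it stands as written. If it is raw, it equals 7.5 / 50 = 15 percentage points, a factor of 2. The sample size is the same either way provided the SD is on the same scale: 7.5 / 10.58 = 15 / 21.16 = 0.71, so n = 32.

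**The case against.** The best defense is that the passage reports thresholds generically from earlier work, never writes 1.5 mm, and uses them only as an interpretive aid. The surrounding text points to the between-group contrast: the primary end point is a difference in change, evidence of effect rests on the group × time interaction, and the limitations section discusses between-group differences. On this view, observed changes is loose wording and not a plan to judge single arms.

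Much of that stands. The article nowhere says that single-arm changes will be tested against 7.5, and the 1.5-mm reading is the least charitable one. But the article itself fixes the number, in a unit that does not match its only described pain intensity scale. The within-arm reading also stays open, because the threshold is called a change and within-group tests are named as a fallback.

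Two stronger readings are tempting and should not be drawn:

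- **That the NDI threshold is on the wrong scale, or trivial.** Points may simply mean percentage points of the 0-100% score. On the plan's own SD, 7.5 is about 0.71 SD, which is not trivial.
- **That the sample size is wrong.** That would need 7.5 and 10.58 to come from different NDI scales. The article gives both as points, in consecutive sentences, for the same instrument, and together they reproduce 32. Nothing suggests a mixture.

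**Conclusion.** The point holds for two things. The pain threshold is not expressed on the recorded scale: taken literally it is 1.5% of the VAS range, one tenth of the 15 mm it would be if the source scale is 0-10. That source scale is an assumption, since the cited study is not available here. The 34% to 41% chance figures rest in addition on an assumed SD of 15 to 25 mm. Second, the plan does not say whether changes are compared with the thresholds within or between arms, and with exercise in both arms the within-arm reading could suggest relevance with no added effect of EDN.

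For the NDI the defect is only an unlabelled unit, with a possible factor of 2.

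The consequence is confined to interpretation. The thresholds do not decide the primary test or define trial success, the pain threshold concerns a secondary outcome, and 32 per group stands if the difference and SD share a scale. It is still worth correcting before results are interpreted.

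**What to change.** 1. Check the cited source and restate the pain threshold in mm on the 0-100 VAS.
2. State in Sample Size Calculation and Data Analysis that 7.5 and 10.58 are on the 0-100% NDI score. If the source shows they are raw, convert both (to 15 and 21.16); n stays 32 per group.
3. State that clinical relevance is judged on the between-group difference in change at postintervention, with its 95% confidence interval, and not on single-arm changes. The interval matters: with the plan's SD and 32 per group, the standard error is 10.58 / 4 = 2.65 and the half-width about 1.96 × 2.65 = 5.2 NDI points (taking 10.58 as the SD of the quantity compared). A point estimate at 7.5 would then still be compatible with a difference of about 2.3.

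The cost is one source check and edits to two sections. Data collection and the primary model do not change. Because Safety Considerations says analyses will not be altered after the first participant is registered, record this as a dated clarification made before group results are seen.
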